#### Outcomes

Primary and secondary outcome are evaluated at T0 and T1.

The primary outcome measures are:1 WISC-III; 2. M-ABC; 3. EQ-i:YV; 4. CBCL 6–18 and Vineland 2.

Secondary outcome measure are: 1. MBT; 2. TOL; 3. BVN5–11; 4. TROG2; and MRI.

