## Methods

### Study design

This is a multicentre interventional single blind randomized controlled study with three groups of children with BIF: group 1- children treated with SST (conventional treatment; *N* = 20); group 2-children treated with the MCNT (experimental treatment, *N* = 20); group 3-children not treated -on the waiting list for SST (no treatment *N* = 20).

The Study was approved by the Ethics Committee of the Don Gnocchi Foundation and of the ASST S. Paolo and S. Carlo Hospital.

All parents signed a written informed consent at the first meeting.

The primary and secondary outcome measures are determined at two time points, within two months prior to the beginning of the treatment (T0) and within two months after the end of the treatment (T1). Evaluations of all children made before and after treatment are performed by two psychologists blind to the type of intervention that the child receives. The flow diagram for study enrollment and randomization, as per Consolidated Standards Of Reporting Trial (CONSORT) guidelines, is shown in Fig. 1.

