### Sample size

For the power calculation, considering preliminary data from our group, we expect a delta of 8 points (T1 –T0) in the primary outcome measure (WISC III FSIQ) between SST and MCNT groups, and 10 points between MCNT and no treatment group with a standard deviation of 10. With a sample size of 60, the calculation of the effect size is 0.43 and the probability is 0.83.

Standard procedures to maintain participants’ interest in the study and to avoid drop outs will be applied (regular meetings with teachers and parents of the children). Moreover, since the MCNT requires children to attend the treatment four day/week, we organized a shuttle that brings them from their school to our Centre brings, to avoid drop-outs.

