### Analysis

Statistical analyses on outcome measures will be conducted using R and SPSS. The General Linear Model (GLM) will be used to test the interaction effects between treatment (MCNT vs no treatment, MCNT vs TAU, TAU vs no treatment) and time (2 repeated measures, T0 and T1). Violations of the parametric model assumptions will be tested and explored with ad-hoc techniques. If violations will be detected, robust methods, data manipulation or statistical corrections will be applied accordingly. An intention-to-treat analysis approach will be used. The missing data process will be examined and the proper imputation method will be selected thereafter.

MRI data will be analyzed with specific statistical software: SPM12, (http://www.fil.ion.ucl.ac.uk/spm/); and FreeSurfer (https://surfer.nmr.mgh.harvard.edu/) and FSL (https://fsl.fmrib.ox.ac.uk/fsl/fslwiki/). Random effect analyses will be done to detect if there is an effect of treatment on the variables measured. The model will comprise a between factor level (group) and a within factor level (time). Demographic characteristics will be used as covariates if associated with the outcome measure.

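### The sample size rests on one primary outcome (FSIQ), but the Outcomes section declares five unranked instruments primary, each open to three contrasts

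*Protocol article*

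**What the plan says.** - **Sample size** refers to one primary measure: "we expect a delta of 8 points (T1 –T0) in the primary outcome measure (WISC III FSIQ) between SST and MCNT groups". The planned difference from the untreated arm is 10 points, and the assumed SD is also 10. The section concludes: "With a sample size of 60, the calculation of the effect size is 0.43 and the probability is 0.83".
- **Background** (closing paragraph on the aim) asks whether MCNT improves global intelligence more than SST. Cognitive abilities and brain development follow as further predictions.
- **Outcomes** states: "The primary outcome measures are:1 WISC-III; 2. M-ABC; 3. EQ-i:YV; 4. CBCL 6–18 and Vineland 2". It names no score within any instrument and gives no order of importance.
- **Analysis** applies a general linear model to the outcome measures, testing treatment-by-time interactions for "MCNT vs no treatment, MCNT vs TAU, TAU vs no treatment". The only corrections it mentions are for violated model assumptions. The article states neither an alpha level nor a multiplicity rule.

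**The concern.** The Sample size and Outcomes sections cannot both describe the same trial. Under the first, FSIQ decides. Under the second, FSIQ is one score within one of five instruments of equal standing. With three contrasts for each instrument there are 5 × 3 = 15 candidate primary tests, and the article does not say how many of them, or which, must succeed.

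Two things are at stake. A significant result on any one instrument in any one contrast could be presented as a positive primary finding, at an error rate well above 5%. And the power statement would cover only one of the declared primaries, because no difference or standard deviation is given for the other four instruments.

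**Working it through.** **Inputs.** From Sample size: differences of 8 (MCNT against SST) and 10 (MCNT against no treatment), SD 10, N = 60. From Study design: 20 per group. From Outcomes: five instruments, or four if CBCL and Vineland 2 count as one. From Analysis: three contrasts. Assumed, because not stated: two-sided alpha 0.05, and a correlation r between instruments of 0 to 0.7.

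**1. The plan's own figure.** The two differences imply mean changes of 0 (no treatment), 10 − 8 = 2 (SST) and 10 (MCNT), with grand mean 4.
- f = √[((−4)² + (−2)² + 6²)/3] / 10 = √(56/3)/10 = 0.432, which matches 0.43.
- Noncentrality λ = f² × 60 = 11.2. The noncentral F with 2 and 57 degrees of freedom at 0.05 gives power 0.839 (0.836 with f = 0.43), against 0.83 stated.

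The figure therefore reproduces as a single unadjusted three-group F-test on FSIQ.

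**2. Power of MCNT against SST.** The standardised difference is 8 / (10 × √(2/20)) = 2.53. Two-sided power at 5% is 0.69 by t-test (38 df), or 0.72 by the normal approximation. It is not 0.83.

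**3. Family-wise error under the global null.** If all 15 tests were independent, the rate would be 1 − 0.95¹⁵ = 0.54. They are not independent, since the contrasts share arms. Simulation with 3 × 20 children, normal change scores, equal correlation between instruments and pooled-variance t-tests (57 df) gives the chance of at least one p < 0.05:

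| Reading | r = 0 | 0.3 | 0.5 | 0.7 |
|---|---|---|---|---|
| 5 instruments × 3 contrasts, ungated | 0.48 | 0.44 | 0.39 | 0.32 |
| 4 outcomes × 3 contrasts, ungated | 0.40 | 0.38 | 0.34 | 0.29 |
| 5 instruments, each gated by an omnibus F-test | 0.23 | 0.21 | 0.19 | 0.15 |
| MCNT against SST only, 5 instruments | 0.23 | 0.21 | 0.18 | 0.15 |

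The r = 0 values in the last two rows agree with 1 − 0.95⁵ = 0.226. For FSIQ alone, three ungated contrasts give about 0.12. With an omnibus F-test first, the rate is about 0.05.

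**4. Keeping five primaries with control.** Bonferroni at 0.05/5 lowers the power of the omnibus F-test on FSIQ from 0.84 to 0.63.

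**The case against.** The strongest reply has four parts.

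- **The deciding question can be inferred.** The Background and Sample size sections together point to FSIQ and to MCNT against SST. This helps in choosing the repair. It does not remove the conflict, because the Outcomes section gives four other instruments the same status.
- **The 15-test count is the least favourable reading.** The stated f and power come from an omnibus test, which suggests that such a test would come first. Gating roughly halves the error rate, and for FSIQ alone it holds the rate at about 5%. This stands, so the gated figures belong beside the ungated ones.
- **Not every rejection would be claimed as success for MCNT.** Five of the 15 tests compare SST with no treatment, and two-sided rejections include MCNT doing worse. The chance of at least one false result favouring MCNT over SST across five instruments is about 0.07 to 0.12. This also stands, but the corresponding one-directional rate for a single test is 0.025, so it is still about three to five times nominal.
- **This is a condensed article.** Multiplicity rules are commonly left to an analysis plan, which is not shown here. A reader might infer that the trial has no error control. The document supports only that none is stated in the article. The contradiction over the primary outcome does not depend on that silence.

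**Conclusion.** The point holds as an internal contradiction: one primary outcome in Sample size, five unranked instruments in Outcomes. If the Outcomes section is followed at an assumed two-sided 5%, the chance of at least one false-positive primary result under the global null is about 32 to 48% ungated (29 to 40% counting four outcomes). It is about 15 to 23% with an omnibus gate on each instrument or with MCNT against SST alone. These ranges rest on the assumed alpha and correlations and on one score per instrument; testing several scores per instrument would raise them.

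A reader might go further and call a false-positive primary result likely. The figures do not support that. Every simulated value is below one half, all assume no effect anywhere, and only the unrealistic case of 15 independent tests passes 50%. Substantially inflated is the right description.

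**What to change.** Revise the Outcomes section so that WISC-III FSIQ is the single primary outcome, in line with the Background and Sample size sections. Move M-ABC, EQ-i:YV, CBCL 6–18 and Vineland 2 to secondary. Then state one decision rule for FSIQ:

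- **Fixed sequence:** MCNT against SST at two-sided 5%, then MCNT against no treatment only if the first succeeds. The first test loses no alpha, but Sample size must restate its power as about 0.69 (difference 8, SD 10, 20 per arm).
- **Omnibus F-test first, then pairwise tests:** with three groups this holds the family-wise rate at about 5% and keeps the basis of the 0.83. That figure is still the power of the F-test, not of MCNT against SST.

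The trial is ongoing and was registered retrospectively, so the change should be a dated amendment made before any unblinded results are seen, with the registry entry brought into line.

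The cost is wording, the loss of primary status for four instruments, and an open statement of the lower power if MCNT against SST alone decides. No extra children or assessments are needed for this repair. If the sponsor prefers to keep several primaries because the treatment targets several domains, that also resolves the conflict, but it needs a stated adjustment and a new sample size calculation with assumptions for each instrument.

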### Analysis

Statistical analyses on outcome measures will be conducted using R and SPSS. The General Linear Model (GLM) will be used to test the interaction effects between treatment (MCNT vs no treatment, MCNT vs TAU, TAU vs no treatment) and time (2 repeated measures, T0 and T1). Violations of the parametric model assumptions will be tested and explored with ad-hoc techniques. If violations will be detected, robust methods, data manipulation or statistical corrections will be applied accordingly. An intention-to-treat analysis approach will be used. The missing data process will be examined and the proper imputation method will be selected thereafter.

MRI data will be analyzed with specific statistical software: SPM12, (http://www.fil.ion.ucl.ac.uk/spm/); and FreeSurfer (https://surfer.nmr.mgh.harvard.edu/) and FSL (https://fsl.fmrib.ox.ac.uk/fsl/fslwiki/). Random effect analyses will be done to detect if there is an effect of treatment on the variables measured. The model will comprise a between factor level (group) and a within factor level (time). Demographic characteristics will be used as covariates if associated with the outcome measure.

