### Participants

Sixty participants will be consecutively recruited from the Child and Adolescent Neuropsychiatry Unit of IRCCS Don Carlo Gnocchi Foundation and of the ASST S. Paolo and S. Carlo Hospital.

Inclusion criteria are: age range between 6 to 11 years old and attending primary mainstream school; with a Full Scale Intelligence Quotient (FSIQ) score ranging from 70 to 85 determined with the Wechsler Intelligence Scale for Children-III (WISC-III) [52, 53]; presence of learning disabilities assessed with the standardized test battery for developmental dyslexia and dysorthographia (DDE-2) [54] and dyscalculia (AC-MT 6–11) [55]; difficulties in executive functions and or verbal comprehension assessed with Modified Barrage bell test (MBT) [56],Tower of London (TOL) [57, 58], and the Test of Reception of Grammar (TROG 2) [59, 60]; presence of an impact on daily life of the above mentioned difficulties as measured by the Child Behavioral Checklist (CBCL 6–18) [61, 62] and Vineland 2 [63].

The exclusion criteria are: presence of major neuropsychiatric disorders (such as ADHD and autism spectrum disorder); presence of neurological conditions such as epilepsy, traumatic brain injury, brain malformations and infectious disease involving the central nervous system. Moreover, the presence of systemic diseases such as diabetes or dysimmune disorders, genetic syndromes such as Down syndrome or Fragile X syndrome and a positive history for psychoactive drugs, particularly referring to current or past use of psychostimulants, neuroleptics, antidepressants, benzodiazepines and antiepileptic drugs are also considered exclusion criteria.

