### Randomization and masking

Randomization in the three groups occurred after screening and baseline assessment (T0). Subjects were randomly assigned to SST or MCNT or no treatment. The randomization process was performed using a computer algorithm (http://graphpad.com/quickcalcs/randMenu/) by an independent operator not involved in neither phase of our research. All evaluations in both pre- and post-treatment are conducted by two psychologists blind to group allocation.

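### With two time points the planned treatment-by-time interaction is a change-score test; adding the T0 score as a covariate is a nearly free gain in precision, small for FSIQ

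*Protocol article*

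**What the plan says.** The Analysis section fixes the model for the clinical outcomes: "The General Linear Model (GLM) will be used to test the interaction effects between treatment" (three pairwise comparisons of MCNT, usual treatment and no treatment) "and time (2 repeated measures, T0 and T1").

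The Sample size section is built on the same quantity: "we expect a delta of 8 points (T1 –T0) in the primary outcome measure (WISC III FSIQ") between SST and MCNT, and "10 points between MCNT and no treatment group with a standard deviation of 10".

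The T0 scores exist before allocation: "Randomization in the three groups occurred after screening and baseline assessment (T0"). Entry requires a "Full Scale Intelligence Quotient (FSIQ) score ranging from 70 to 85".

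The only sentence on covariates stands in the MRI paragraph of the Analysis section: "Demographic characteristics will be used as covariates if associated with the outcome measure". Nowhere does the article name the baseline value of the outcome itself as a covariate.

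**The concern.** A change score subtracts the whole of the T0 score, as if a child one point higher at T0 were expected to be one point higher at T1. Test scores contain measurement error, so a slope below 1 is plausible for these instruments. Two things follow when the slope is b < 1:

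- The change score carries noise from T0 that a fitted slope would remove.
- A chance difference between arms at T0 is over-corrected. Each point of difference moves the estimated contrast by (1 − b) in the opposite direction.

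With 20 children per arm such differences will occur. MCNT versus SST is the trial's main question, and its power on the article's own inputs is about 0.70. Precision available from data already collected is therefore worth having.

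**Working it through.** **Inputs from the article.** 20 children per arm, 60 in all (Study design). Differences in mean change of 8 points (MCNT versus SST) and 10 points (MCNT versus no treatment), SD 10, read as the SD of the change (Sample size). Entry FSIQ 70 to 85 (Participants).

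**Assumptions.** Two-sided alpha 0.05, which is not stated but reproduces the stated power. The T0–T1 slope or correlation is not given, so a range is shown.

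**1. The article's own figure.** Mean changes of 10, 2 and 0 have mean 4 and variance (36 + 4 + 16)/3 = 18.67, so f = √18.67/10 = 0.432. The noncentral F with 2 and 57 df and λ = 60f² gives power 0.836 at f = 0.43 and 0.839 unrounded. The article states 0.43 and 0.83. The trial is thus sized on the three-group test of change scores.

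**2. The interaction is the change-score test.** On simulated data with three arms of 20 and two time points, the interaction F and the one-way ANOVA F on T1–T0 were both 6.0403 (p = 0.00418).

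**3. MCNT versus SST as planned.** Noncentrality is 8/(10 × √(2/20)) = 2.53. Power is 0.701 with error pooled over three arms (57 df), or 0.693 from the two arms alone (38 df).

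**4. ANCOVA with T0 as the only covariate.** Residual variance = Var(change) − (1 − b)² × SD₀², where SD₀ is the baseline SD. Estimating the slope multiplies the variance by about 1 + 1/55 = 1.018 and leaves 56 df.

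*FSIQ.* A normal(100, 15) distribution cut to 70–85 has SD₀ = 4.05 (variance 16.37). A uniform distribution would give 15/√12 = 4.33.

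| Slope b | Residual variance | × 1.018 | Power, 8 points |
|---|---|---|---|
| 0.3 | 100 − 0.49 × 16.37 = 91.98 | 93.65 | 0.729 |
| 0.4 | 94.11 | 95.82 | 0.719 |
| 0.5 | 95.91 | 97.65 | 0.711 |
| 0.7 | 98.53 | 100.32 | 0.699 |
| 0.9 | 99.84 | 101.65 | 0.694 |
| 1.0 | 100 | 101.82 | 0.693 |

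With SD₀ = 4.33 the powers at b = 0.3, 0.5 and 0.7 are 0.734, 0.714 and 0.700.

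*Outcomes without a numerical entry range.* With equal SDs s at T0 and T1, Var(change) = 2s²(1 − ρ) and the ANCOVA variance is s²(1 − ρ²), so the ratio is (1 + ρ)/2. The standardised change effect is assumed to be 0.8; the article gives no effect for these outcomes.

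| ρ | Ratio | Ratio × 1.018 | Power |
|---|---|---|---|
| 0.5 | 0.75 | 0.764 | 0.812 |
| 0.7 | 0.85 | 0.865 | 0.762 |
| 0.9 | 0.95 | 0.967 | 0.715 |

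The comparison value is again 0.701.

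**5. Chance imbalance.** The SD of the FSIQ baseline difference between two arms is 4.05 × √(2/20) = 1.28 points. A 2-point gap is therefore about 1.6 SDs. At b = 0.5 it shifts the change-score contrast by 0.5 × 2 = 1 point, against the planned 8.

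**The case against.** The strongest reply is that nothing is stated wrongly. The change-score test is unbiased over randomisation and is the very test on which the trial was sized. This stands, and it limits the point to an improvement.

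The second reply is that FSIQ, the only outcome with planning figures, gains little and may lose slightly. This also stands: from b of about 0.7 upward there is no gain, and at b = 1 power falls from 0.701 to 0.693.

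Third, adding age and centre as well could undo the gain. If they explain nothing, the three-covariate model with pooled error has 54 df and variance inflation of about 1 + 3/53. FSIQ power is then 0.703 at b = 0.4 and 0.694 at b = 0.5, essentially the change-score value. Using two arms only (35 df, inflation 1 + 3/34) it is 0.681 and 0.673, below 0.693. Those covariates should therefore not be required here. The covariate sentence in the MRI paragraph may in any case have been meant to cover age, and the full covariate list may stand in a document that is not shown.

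A reader might also infer that selecting children on low scores biases the planned contrast through regression to the mean. The documents do not support that. Selection on T0 FSIQ does not itself lower the slope of T1 on T0, and regression to the mean is expected equally in all randomised arms, so it cancels in the contrast.

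None of this removes the case for adjusting for T0 alone, where the possible loss is very small.

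**Conclusion.** The point holds as a free improvement, not as an error. The planned interaction is a valid change-score comparison. ANCOVA on T0 has a residual variance that is never larger apart from a cost of about 2% for estimating the slope, and it removes the shift of (1 − b) per point of chance baseline difference.

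For FSIQ the gain in MCNT versus SST power is at most a few points: from 0.70 to 0.71–0.73 at slopes 0.5–0.3, and none from about 0.7. This rests on SD 10 for the change and a baseline SD of about 4.05.

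For M-ABC, EQ-i:YV, CBCL and Vineland, whose entry range is not bounded by numbers, the gain could be larger: 0.81, 0.76 and 0.71 at correlations 0.5, 0.7 and 0.9, against 0.70. A reader might take these as the gain for the sized FSIQ contrast. They are not: they belong to an outcome with an assumed effect of 0.8 and equal SDs, neither of which the article gives.

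**What to change.** For each clinical outcome, replace the interaction test by a linear model of the T1 score on treatment arm, with the T0 score of the same measure as a pre-specified covariate. Fit it to all three arms together, keep the same three contrasts, and report adjusted mean differences with 95% confidence intervals. A longitudinal model with a common T0 mean across arms is an equivalent choice. Age and centre may be added if the sponsor expects them to explain variance, but they are optional and should be fixed in advance.

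The cost is a change of wording in the Analysis section, one degree of freedom and about 2% in variance. No new data are needed and the sample size does not change. The article reports the trial as ongoing, so the change should be dated and made before outcome data are examined by arm.

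### The Analysis section defers the imputation method, the remedy for model violations and the MRI covariates until the data are seen, without saying these choices are made blind to arm

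*Protocol article*

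**What the plan says.** All the relevant statements are in the Analysis section of the protocol article.

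- **Model:** "The General Linear Model (GLM) will be used to test the interaction effects between treatment" and time, with three pairwise comparisons and two time points, T0 and T1.
- **Assumptions:** "Violations of the parametric model assumptions will be tested and explored with ad-hoc techniques". The response is: "If violations will be detected, robust methods, data manipulation or statistical corrections will be applied accordingly".
- **Analysis set:** "An intention-to-treat analysis approach will be used".
- **Missing data:** "The missing data process will be examined and the proper imputation method will be selected thereafter".
- **Covariates**, in the paragraph on MRI data: "Demographic characteristics will be used as covariates if associated with the outcome measure".

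The section gives no default imputation method, no trigger or order for the remedies, and no list of covariates or criterion for association. The Randomization and masking section blinds the two assessing psychologists and does not mention whoever chooses the analysis. The Trial status section reports the trial as ongoing, so on the article's own account the rules could still be fixed.

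**The concern.** These sentences are more than silence that an analysis plan would fill. They state that the choice comes after the data have been examined, so a later plan that fixed the methods would have to replace this text.

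Two things are at stake. First, if the person choosing can see results by arm, several defensible analyses are available for each comparison and the nominal error rate is no longer assured. Second, the missing-data choice can affect the estimate itself. MCNT asks for three hours a day over nine months. The comparators are two 45-minute sessions a week or a waiting list. The Sample size section treats drop-out as a risk worth countering with a shuttle and regular meetings. Loss could therefore differ by arm and be related to response. Observed data cannot show whether missingness depends on the unseen T1 score, so examining the missingness cannot by itself identify the proper method.

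**Working it through.** **1. The plan's own figure.** The Sample size section states: "we expect a delta of 8 points (T1 –T0) in the primary outcome measure (WISC III FSIQ) between SST and MCNT groups". For MCNT against the untreated arm it assumes a 10-point difference, and it takes the SD as 10. Taking mean changes of 2 (SST), 10 (MCNT) and 0 (no treatment):

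- The grand mean is 4, and the mean squared deviation is (4 + 36 + 16)/3 = 18.67.
- f = √18.67 / 10 = 0.432, against the stated 0.43.
- One-way ANOVA on change with N = 60, three groups and two-sided alpha 0.05 (assumed; the article states none) gives power 0.836 at f = 0.43, against the stated 0.83.

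The stated power reproduces and does not depend on this point.

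**2. Type I error when the analysis is chosen late.** These are null simulations with two arms of 20 at nominal 5%.

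| How the analysis is chosen | Normal data | Skewed data |
|---|---|---|
| One t test fixed in advance | 4.8% | 4.9% |
| Normality pretest, then t or rank test | 5.0% | 5.3% |
| Covariates entered if associated with the outcome | 4.9% | 5.5% |
| Smallest p of t, rank and log-transformed tests | 6.4% | 7.2% |
| Smallest p over covariate sets | 7.5% | 8.1% |
| Smallest p over those tests and covariate sets | 8.4% | 9.8% |

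A harsher set on normal data takes the smallest p of a t test, Mann–Whitney, 20% trimmed t test, and t test after dropping values beyond 2 SD. It rejects in about 11% of trials. Removing values beyond 2 SD is an illustration and appears nowhere in the article.

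Rule-based choice stays near nominal, and inflation needs selection on p-values. Assumption tests are also a weak gate at this size: with 20 observations, Shapiro–Wilk detected moderate skew (gamma, shape 4) in only 29% of samples.

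**3. Missing data.** Choosing by p-value between complete-case analysis and zero-change imputation, with 15% missing completely at random, gave 5.1% (normal) and 5.4% (skewed), which is little inflation. The estimate is more sensitive. Assume 20% loss in MCNT and 5% in SST.

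- *Loss unrelated to response.* Complete cases estimate 10 − 2 = 8.0. Zero-change imputation estimates 0.80 × 10 − 0.95 × 2 = 8.0 − 1.9 = 6.1.
- *Poorer responders likelier to leave MCNT, true effect 8 (simulated).* The mean estimates are 10.3 (complete case) and 7.9 (zero change). The two disagree on significance in 12.7% of trials.
- *Same informative loss under the null.* Rejection is 11.7% (complete case), 8.7% (zero change) and 12.0% for the better of the two. At 30% MCNT loss the figures are 17.5%, 10.1% and 17.9%.

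In the last case almost all the excess is bias from drop-out, and choosing between methods adds little (11.7% to 12.0%). Fixing one method in advance would not remove it.

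**4. What a fixed baseline-adjusted model offers.** With SD of change 10 and T0–T1 correlation ρ (assumed), the residual variance after adjusting for T0 is 100 × (1 + ρ)/2, which is 80 at ρ = 0.6 and 90 at ρ = 0.8. For 8 points and 20 per arm, power rises from about 70% for the treatment-by-time test to about 74% (ρ = 0.8) or 78% (ρ = 0.6). T0 is measured before randomisation, so the adjustment is legitimate.

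**The case against.** The strongest reply is that the article never says choices will follow treatment results. It speaks of examining the missing-data process and of acting if violations are found. Both can be done without looking at arm differences, and rules of that kind hold the error rate near 5%. Details such as covariate lists and analyst masking commonly sit in an analysis plan, which is not shown here. The covariate sentence is itself a rule stated in advance; it concerns MRI, a secondary outcome, and conditions on association with the outcome, not on the treatment effect. The term data manipulation, listed beside robust methods and corrections, most plausibly means transformation.

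Most of this stands. It rules out saying that the plan inflates false positives, and the 11% figure is only an upper illustration. It does not remove the point that the article positively places these choices after the data are examined, with no order, default or blinding.

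A reader might also infer that late choice of imputation defeats the intention-to-treat commitment, because a two-time-point model has nothing from a child without T1. The document does not support that. Whether the child is retained depends on whether T1 is imputed, not on when the method was picked, and the article commits both to intention-to-treat and to imputation.

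**Conclusion.** The point holds as one about deferred choices with no safeguard, and it should be corrected. The possible cost to type I error runs from essentially none (a fixed rule, about 5%) to about 11% (smallest of four p-values, 20 per arm, normal data). The text permits the upper end but does not describe it. The missing-data choice could shift the MCNT–SST estimate by about 2 points against a planned 8. That rests on assumed losses of 20% and 5%, on two deliberately simple methods and, for the informative case, on an assumed link between poor response and leaving MCNT. The article gives no drop-out rates. Neither the stated power nor N = 60 changes.

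**What to change.** Before T1 data are seen by arm, amend the Analysis section or settle the following in the analysis plan:

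1. **Primary model.** For each primary measure, use ANCOVA of T1 adjusted for T0, kept whatever the assumption checks show. Add robust standard errors or a permutation test as a sensitivity analysis. Replace the term data manipulation with any transformation actually intended, by name.
2. **Missing data.** Name one default method, valid if data are missing at random, using T0 and baseline variables for all randomised children in their assigned arm. Fitting separate imputation models within arms of 20 would be fragile and is not needed. Add a delta-adjusted sensitivity analysis that makes the imputed outcomes of MCNT drop-outs progressively worse. A missing-at-random method cannot remove bias from informative drop-out, and this analysis shows how much of it the conclusion could withstand.
3. **MRI covariates.** Replace the association condition with named covariates, such as age and sex.

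If any choice must stay open, state that it will be made blind to arm. The cost is wording, a little more analysis work and the loss of after-the-fact flexibility. The sample size is unaffected.
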